### 4.2 Inclusion criteria

1. Resident of one of the participating care facilities
2. Age of majority
3. Written declaration of consent
4. Consent of the guardian for residents who are not capable of giving consent

### 4.3 Exclusion criteria

1. Persons who are accommodated in an institution on the orders of the authorities or the courts.
2. Persons who are in a dependent or employment relationship with the investigator

## 5 Trial treatments and procedure

If a patient voluntarily consents in writing to participate in the trial and is eligible for participation according to all inclusion and exclusion criteria, the patient will be assigned a unique patient number that will be used to further identify all information collected on that patient from then on.

### 5.1 Project procedure

#### *Virtual digital counter*

Optimal@NRW initially relies on the already known and proven pillars of medical care (general practitioners, KV emergency service, rescue service), but expands them with a telemedical component. In a medical emergency situation, in which the immediate medical assistance by the emergency service does not have to take place, an upstream, intersectoral, telemedical instrument is used at the level of care facilities within the framework of Optimal@NRW.

| Principal investigator    | Trial centre                                                  | CTC-A No. |
|---------------------------|---------------------------------------------------------------|-----------|
| [name] | Central Emergency Department, RWTH Aachen University Hospital | 19-019    |

The first step is to contact the emergency hotline of the Association of Statutory Health Insurance Physicians (116 117). The dispatcher first carries out a software-supported structured initial medical assessment using SmED (Structured Initial Medical Assessment in Germany).

[figure not shown]

(Source: Central Institute for Statutory Health Insurance Physicians in Germany: <https://www.zi.de/smed/>)

Figure 4: Overview SmED workflow

The next steps in care provision within the cooperation network between the nursing facility, general practitioners, the NRW Physicians' Call Centre and the portal practice of the Association of Statutory Health Insurance Physicians of North Rhine-Westphalia (Kassenärztliche Vereinigung Nordrhein), which is currently being set up, the central emergency room of the RWTH Aachen University Hospital and the rescue services of the Aachen region are then examined, coordinated and initiated. The decisive factor is that the system builds on structures already established in standard care (see Figure 1 "green arrows") and supplements them with an intersectoral usable consultation and documentation system as well as the possibility of transferring measures that can be delegated by a doctor to a non-medical assistant (see below) (see Figure 1 "orange arrows").

[figure not shown]

## Test plan -Optimal@NRW-

V03, 15.02.2022

| Principal investigator    | Trial centre                                                  | CTC-A No. |
|---------------------------|---------------------------------------------------------------|-----------|
| [name] | Central Emergency Department, RWTH Aachen University Hospital | 19-019    |

### *Early warning system*

As a supplementary component, a so-called early warning system (EWS) is implemented. With a voluntary daily and non-invasive measurement of certain vital values (e.g., blood pressure, pulse, oxygen saturation, temperature) on a so-called spot check monitor, the data obtained are compared within the EWS. In the event of an abnormality that indicates an imminent deterioration of the health condition, the EWS alerts the telemedicine unit of the RWTH Aachen University Hospital emergency room, in addition to the responsible nurse. In the best case, the developing medical problem is detected, before it becomes relevant and the resident is treated before he or she falls ill and, in the worst case, would have to be treated as an inpatient.

The EWS is already approved as a medical device and is only used within the scope of its approval.

Within the framework of the early warning system, the practicability of biosensors is to be investigated. Using a sensor system that is fixed to the skin (usually in the area below the collarbone) by means of a patch and left there for several days, vital parameters such as heart rate and rhythm, respiratory rate, oxygen saturation can be continuously detected and transmitted wirelessly to a monitoring station. Rare side effects to be expected from the systems known on the market consist of a potential intolerance to the patch, even though it is generally well tolerated. In order to exclude such intolerance, patients are asked about any known patch allergies. If a patch allergy is known, no biosensors are applied to this resident.

### *Non-medical assistance*

If the need for a delegable activity becomes apparent during a teleconsultation (e.g., insertion of a transurethral bladder catheter), this activity can be performed by a non-medical assistant (m/f/d). The specially trained nurses are stationed at the Emergency Department of the RWTH Aachen University Hospital and are delegated to the respective nursing facility by car according to the doctor's orders (general practitioner, KV service, tele doctor of the RWTH Aachen University Hospital). For the Optimal@NRW project, training of the staff is specifically geared to the requirements of the project, in order to ensure a securely mastered implementation competence.

### *Teleconsultation system*

Technically, a bidirectional communication structure is set up within the Optimal@NRW system, which enables data exchange in addition to communication in image and sound. This teleconsultation system consists of a mobile stand, i.e., mobile into each resident's room, which is connected to the IT infrastructure via LAN/WLAN or mobile radio. The system is equipped with a monitor/input device combination for the nursing staff.

[figure not shown]

## Test plan -Optimal@NRW-

V03, 15.02.2022

| Principal investigator    | Trial centre                                                  | CTC-A No. |
|---------------------------|---------------------------------------------------------------|-----------|
| [name] | Central Emergency Department, RWTH Aachen University Hospital | 19-019    |

The doctor participating in the teleconsultation is displayed here by video. Furthermore, the patient's already stored data (electronic patient documentation and file) are displayed. The tele doctor's orders are transmitted in written form in conformity with the law. A conversation between the nurse and the tele doctor takes place via a monitor loudspeaker system. The participating tele doctor is displayed to the patient via another monitor facing the resident. The tele doctor can also communicate with the patient via camera and loudspeaker/monitor. To record and display vital parameters in real time, the telecommunication system provides for the recording of blood pressure, peripheral oxygen saturation, ECG and temperature.

The Philips device used to record and transmit vital signs is approved as a medical device and is only used within the scope of its approval. This medical device is integrated into the overall software of the Docs in Clouds teleconsultation system.

### *Central electronic patient record*

A central electronic patient record is also implemented, which can be viewed by all partners involved in the patient's treatment. Important medical information for the entire cooperation network is available there and can be integrated during treatment. Orders can be made in writing by the attending physician and their execution can be documented by the responsible nurse or non-medical assistant.

The medical decisions and measures taken as part of the teleconsultation, as well as the prescribed medication, are documented and stored in a central electronic patient record in accordance with the currently valid data protection regulations.

If the teleconsultation was carried out, for example, by the emergency physician of the emergency room at the University Hospital RWTH Aachen and not by the treating family doctor, the latter is informed accordingly by the system. This means that he or she not only has the possibility to inspect and check the measures carried out, but can also coordinate the further therapy steps and, if necessary, follow and shape the medical course by means of another teleconsultation.

## 6 Data collection

The following data will be collected at the beginning of the trial:

- Written consent
- General information about the resident (health insurance, legal care, name of the nursing home, family doctor, power of attorney/ living will, etc.)
- Demographic data (name, age, gender, ethnicity, etc.)
- Medical information about the resident (previous illnesses, allergies, home medication, ECG, vaccinations, etc.)
- Size, weight

[figure not shown]

## Test plan -Optimal@NRW-

V03, 15.02.2022

| Principal investigator    | Trial centre                                                  | CTC-A No. |
|---------------------------|---------------------------------------------------------------|-----------|
| [name] | Central Emergency Department, RWTH Aachen University Hospital | 19-019    |

- Survey of doctor contacts and hospital admissions retrospectively since the start of the study (at the earliest from 01.05.2021).
- Quality of life surveys
- more

The following data are collected during the control phase/transition phase/intervention phase:

- Hospitalisation (number of hospital days, admission diagnosis, etc.)
- Visit to family doctor, specialist, etc. (date, duration, occasion, etc.)
- Rescue service mission (date, occasion, etc.)
- more

The following data will be collected during the intervention phase:

- Early Warning System data
  - Blood pressure
  - Heart rate
  - Oxygen saturation
  - Temperature
  - Respiratory rate (when using biosensors)
  - more
- Tele visit:
  - Reason for the tele visit
  - Time of request, start and end of the tele visit
  - Output of the tele visit
    - Use of the non-medical assistant
  - Content of the tele visit
    - Survey according to medical practice and symptoms
      - Vital data
      - Vigilance
      - Fast Test
      - Pupil status
      - Auscultation
      - Indication of delirium
      - 12-channel ECG
  - more

The following data is collected in the event of a drop-out:

- Reason for leaving
  - Death
  - Transfer to another nursing home, if this is not part of the Optimal@NRW project.
  - Withdrawal of the declaration of consent
  - more

[figure not shown]

## Test plan -Optimal@NRW-

V03, 15.02.2022

| Principal investigator    | Trial centre                                                  | CTC-A No. |
|---------------------------|---------------------------------------------------------------|-----------|
| [name] | Central Emergency Department, RWTH Aachen University Hospital | 19-019    |

These data will be collected in a trial database by the nursing staff as well as by the other medical service providers participating in the project. These data will be supplemented by routine data from the participating health insurance funds from 2019, which they will make available for the participating insured persons. The preliminary observation period of two years is intended to determine the relevant baseline characteristics of the patients.

The data from the central electronic patient record are transferred to a study database. By means of a trusted third party, the primary data are pseudonymised and another pseudonym key is made available to the health insurance funds. The merging of the data sets takes place at the evaluation centre in pseudonymised form.

## 7 Safety data, records and notifications

Patient safety is monitored and assessed through regular monitoring and a Safety Board.

### 7.1 Safety Board

The Safety Board decides whether the safety of the patients is still guaranteed. The Safety Board consists of independent doctors who are not involved in the implementation of the project. The Safety Board is alerted in case of the following events:

- Resuscitation during teleconsultation
- Unexpected death during teleconsultation
- Unexpected death within 24 hours of a teleconsultation
- Unexpected hospitalisation within 24 hours of a tele-consultation
- Unexpected death while wearing a biosensor (if available)

### 7.2 Documentation of events that could potentially jeopardise patient safety

Adverse events or serious adverse events are documented, evaluated and reported in accordance with GCP and the Professional Code of Conduct for Physicians (BOÄ).

## 8 Termination of trial

The trial participation of an individual trial participant can be terminated prematurely, if one of the following criteria is fulfilled:

- Serious adverse events that do not allow the continuation of the trial
- Lack of compliance
- The trial participant withdraws the declaration of consent

The reason, timing and specific details of a participant's withdrawal from the trial are recorded on a separate page of the CRF (comments page). The investigator should specify a primary reason for the participant's withdrawal from the trial.

All safety-relevant data are collected and reported until the trial participant withdraws from the trial.

[figure not shown]

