## Test plan -Optimal@NRW-

V03, 15.02.2022

| Principal investigator    | Trial centre                                                  | CTC-A No. |
|---------------------------|---------------------------------------------------------------|-----------|
| [name] | Central Emergency Department, RWTH Aachen University Hospital | 19-019    |

Any decision regarding early trial termination for a trial participant or his/her exclusion will be discussed in advance with the clinical trial director. Dropout trial participants will be replaced.

The entire trial may be discontinued if one of the following criteria is met:

- The benefit-risk assessment on which the trial is based changes in such a way that the risks outweigh the benefits and/or the potential risks are no longer justifiable.
- Administrative problems that prevent the proper conduct of the trial.
- Serious protocol violations

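### Section 8 lets residents be removed for undefined non-compliance or for certain SAEs without providing for hospital days afterwards, so removal could differ by phase and can bias the primary comparison

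*Protocol*

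**What the plan says.** Section 8 lists three grounds on which an individual's participation can be ended early. Besides withdrawal of consent they are "Lack of compliance" and "Serious adverse events that do not allow the continuation of the trial". Compliance is not defined, and neither ground is tied to a phase. The decision is discretionary: "Any decision regarding early trial termination for a trial participant or his/her exclusion will be discussed in advance with the clinical trial director". The reason and timing are recorded, and "Dropout trial participants will be replaced".

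On data after removal, section 8 says only this: "All safety-relevant data are collected and reported until the trial participant withdraws from the trial". In section 6, the list headed "The following data is collected in the event of a drop-out" covers the reason for leaving and names no further outcome follow-up. The same section says that the trial data are "supplemented by routine data from the participating health insurance funds from 2019", for participating insured persons. It does not say whether this continues once a resident has been removed.

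The early warning system in section 5.1 works "With a voluntary daily and non-invasive measurement of certain vital values". The synopsis compares control-phase with intervention-phase data, and section 2.1 makes hospital days the primary outcome.

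**The concern.** The intervention is given to whole homes, and the question is its effect on hospital days among their participating residents. That needs the same residents to be observed in the same way on both sides of crossover. Section 8 does not separate stopping an intervention component from stopping observation. Teleconsultation, vital-sign measurement and the biosensor all start at crossover, so most of what a resident could fail to comply with exists only from then on. Staff know which phase their home is in, and the removal decision is a judgement.

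If residents who refuse or cannot manage these components, or who have a serious event, leave observation mainly in the intervention phase, and if their hospital use differs from that of the others, the intervention-phase mean moves without any effect of the intervention. An analysis plan can define analysis sets, but it cannot restore hospital days that were never collected.

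**Working it through.** **The plan's own dropout figures.** Section 10.1 takes 43 residents per home and interval and 12% dropout per quarter: 43 / 0.88 = 48.9, rounded to 49, so about 6 replacements per home and quarter. With the 24 homes of section 4.1 and 8 quarters: 43 × 24 = 1,032; 6 × 24 × 8 = 1,152; total 2,184, as stated. The 12% is not split by reason or phase. It therefore does not show how many removals for non-compliance or SAEs are expected, or when.

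**Relative size.** The inputs below are assumptions and are not in the protocol.
- x: share of intervention-phase person-quarters lost through removal. None is lost in control.
- r: hospital days of those residents, as a multiple of the average over all intervention-phase residents.
- The lost quarters are not recovered from any source, and replacements resemble the residents who stay.

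The observed mean is the true mean times (1 − x·r)/(1 − x), so the spurious reduction is 1 − (1 − x·r)/(1 − x) = x(r − 1)/(1 − x).

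| x | r = 0.5 | r = 1 | r = 2 | r = 3 |
|---|---|---|---|---|
| 1% | −0.5% | 0 | 0.01/0.99 = 1.0% | 0.02/0.99 = 2.0% |
| 5% | −2.6% | 0 | 0.05/0.95 = 5.3% | 0.10/0.95 = 10.5% |
| 10% | −5.6% | 0 | 0.10/0.90 = 11.1% | 0.20/0.90 = 22.2% |

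A negative entry is a spurious increase. Against the planned 30%, 5.3% is 18% of the target effect, 10.5% is 35% and 11.1% is 37%. The corner at x = 10% and r = 3 is the least plausible and is not relied on. If replacements had the average of all residents, the formula would be x(r − 1), and these three values would become 5%, 10% and 10%.

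**Size in days, with smaller differences.** Let D be the excess of removed residents over the mean of all intervention-phase residents. The shift is x/(1 − x) × D. The planned difference is 13.22 − 9.25 = 3.97 days per quarter. D from 1 to 8 days is a milder assumption than r = 2: on a mean of 13.22 it means r from 1.08 to 1.61.

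| x | D = 1 | D = 3.97 | D = 8 |
|---|---|---|---|
| 1% | 0.01 | 0.04 | 0.08 |
| 5% | 0.05 | 0.21 | 0.42 |
| 10% | 0.11 | 0.44 | 0.89 |

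The largest value, 0.89 days, is 22% of 3.97.

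**Effect on the test.** A Hussey-Hughes model with 24 homes, 8 periods, transition cells dropped, SD 4.5, ICC 0.12 and 43 residents per home-period gives a standard error of 0.26 days. A constant shift in all intervention cells passes in full to the estimated effect. With no true effect, a nominal two-sided 5% test then rejects at 5.0 to 6.1% for x = 1%, 5.5 to 36% for x = 5%, and 7 to 92% for x = 10%, across D = 1 to 8. These rates depend on that small standard error; a larger one would make the inflation smaller.

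**The case against.** Four stronger readings are tempting, and the document does not support them.

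- A reader might infer that non-compliance can arise only once the intervention runs. Section 8 names no phase. Section 11.2.1 obliges participants to carry an ID card throughout, and section 11.2 refers to participant responsibilities in general. Mainly is defensible; only is not.
- A reader might infer that any SAE leads to removal. The ground is limited to events that do not allow continuation. A Safety Board alert under section 7.1, which includes unexpected hospitalisation within 24 hours of a teleconsultation, is not itself a ground for removal.
- A reader might infer that outcome collection stops at removal. The text is silent rather than explicit, and insurer data could fill the gap.
- A reader might fault replacement as such. It belongs to the open cohort (section 3.1), with permanent recruitment (section 4.1) and a planned 12% dropout. Nothing says that earlier data are deleted.

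It can also be argued that a voluntary measurement cannot be a matter of compliance, that a known patch allergy leads only to no biosensor being applied, and that termination is discussed with the trial director and its reason recorded. Analysis sets may be defined in an analysis plan that is not shown.

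These points limit the claim to what can happen. They do not remove the gap. An undefined ground combined with a voluntary component leaves it open who may be removed, discussion with the director does not prevent selection, and no section secures hospital days after removal.

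**Conclusion.** The point holds as a route to bias, not as a demonstrated bias. As written, section 8 permits discretionary removal that could differ by phase and be related to the primary outcome, with no stated follow-up for hospital days.

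Bias needs three conditions together: unequal removal by phase, a difference in hospital days between removed and remaining residents, and loss of the later data. If any one is absent, it is zero. The protocol gives no removal rate, so neither size nor direction can be derived from it. With removal in the intervention phase only and nothing retained, the distortion is negligible at about 1%. It is a spurious reduction of roughly 5 to 11% for x = 5% at r = 2 or 3 and for x = 10% at r = 2. It favours control if removed residents have fewer hospital days.

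Sections 5.1 and 8 must be reconciled on whether declining a voluntary measurement can count as non-compliance. The correction is cheap and uses data links already planned, while outcome days not collected may not be recoverable later, so it should be made.

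**What to change.** Amend section 8, with a matching sentence in section 6:

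1. Delete lack of compliance as a ground for ending trial participation or observation. This also resolves the tension with the voluntary measurement in section 5.1.
2. State that stopping an intervention component, for whatever reason, does not end the collection of hospital days and death. These continue to come from the home's record and the linked insurer data unless consent to data use is withdrawn. The home's record is needed as well, because insurer data come only from participating funds.
3. State that the resident is analysed in the home's scheduled phase.
4. Keep replacement as open-cohort recruitment, and state that data of the resident who left are retained.

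When a component is stopped for a resident remains a clinical matter that this change does not touch. The total of 2,184 is unaffected. The cost is amendment wording, with resubmission to the ethics committee, and a little more routine follow-up.

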### 2.2 Secondary target parameters

Secondary target parameters are:

- ICU length of stay
- Organ failure
- Mortality
- Hospital length of stay with regard to main diagnosis through telemedical visit after discharge
- Number of hospitalizations for ambulatory care-sensitive conditions (ACSH)
- 30-day survival/hospital survival
- nosocomial infections
- other

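### Section 8 ends safety collection at any early exit, so the outcome of an SAE that caused the exit, and Safety Board trigger events later in the 24-hour window, fall outside it

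*Protocol*

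**What the plan says.** Protocol section 8 (Termination of trial) gives three grounds for ending one resident's participation early: "Serious adverse events that do not allow the continuation of the trial", lack of compliance, and withdrawn consent. It then says that "The investigator should specify a primary reason for the participant's withdrawal from the trial", and sets the end of safety ascertainment: "All safety-relevant data are collected and reported until the trial participant withdraws from the trial".

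Section 7.1 (Safety Board) lists the events that must be brought to the Board. Two of them are defined by a time window: "Unexpected death within 24 hours of a teleconsultation" and "Unexpected hospitalisation within 24 hours of a tele-consultation". The window runs from the teleconsultation. Nothing is said about residents whose participation has ended in the meantime.

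Section 7.2 adds a general rule: "Adverse events or serious adverse events are documented, evaluated and reported in accordance with GCP" and the professional code for physicians. It names no follow-up period.

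Section 6 (Data collection) has a list introduced by "The following data is collected in the event of a drop-out". The item named there is the reason for leaving, with death, transfer to a home outside the project, withdrawn consent and an open-ended entry beneath it. No safety follow-up is named.

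**The concern.** Withdrawn consent can justify ending data collection. Termination by the investigator because of an SAE is a different case: how that event ended is the most important safety fact about that resident. Section 8 gives both cases the same end point.

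The Safety Board judges whether patients remain safe, and section 8 allows the whole trial to be stopped if the benefit-risk assessment turns unfavourable. Both depend on trigger events and SAE outcomes being reported completely. A rule that ends collection at exit can remove information about residents who left because something went wrong. This is a rule that the protocol states, so it is not a detail left to a later analysis plan.

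**Working it through.** No arithmetic applies, and there is no planned figure to reproduce. The check compares the provisions.

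1. **What section 8 means by withdrawal.** It lists three grounds for early termination and then asks for a primary reason for the participant's withdrawal. Asking for a reason makes sense only if the word covers more than withdrawn consent. The natural reading is that withdrawal means any early exit, including one caused by an SAE.

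2. **Where safety collection ends.** Section 8 places the end at withdrawal. It makes no distinction by ground and states no later follow-up.

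3. **Where the Safety Board window ends.** Section 7.1 places it 24 hours after the teleconsultation, without reference to participation status.

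4. **Cases, on the reading in step 1:**

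| Exit | Section 8 | Section 7.1 |
|---|---|---|
| Terminated for an SAE, more than 24 hours after any teleconsultation | Collection ends at exit; the later outcome of the SAE falls outside it | No 24-hour trigger applies |
| Terminated for an SAE or lack of compliance, less than 24 hours after a teleconsultation; unexpected death or unexpected hospitalisation follows within the window | Collection has ended | Alert required |
| Consent withdrawn less than 24 hours after a teleconsultation; same later event | Collection has ended | Alert required, no exception stated |

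The first row is a gap in SAE follow-up. The second and third rows are the direct conflict between the end points in sections 7.1 and 8.

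5. **Whether another provision closes the gap.**
- Section 7.2 refers to GCP in general terms. It gives no follow-up period and does not displace the specific end point in section 8.
- The drop-out list in section 6 names no safety outcome after exit.
- Section 9 returns participants to usual care and adds no follow-up.
- The insurers' routine data in section 6 are merged in pseudonymised form at the evaluation centre. The protocol describes no route from there to the Safety Board.

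6. **Size.** The direct conflict needs an exit within 24 hours of a teleconsultation and a later unexpected event inside the same window. The protocol gives no expected number of teleconsultations, SAE-driven exits or trigger events, so no frequency can be calculated.

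**The case against.** The strongest reply has four parts.

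- **The sentence sets a minimum and is not a ban.** Collecting until withdrawal does not forbid reporting afterwards. A site that alerts the Board after an exit satisfies section 7.1 and breaches nothing in section 8. This stands. A reader might infer that a site cannot comply with both sections; the text does not support that. What remains is two different end points and no statement of which governs.
- **The word may be meant narrowly.** The sentence has the participant as the one who withdraws, as does the third ground, withdrawn consent. On that reading collection stops only when consent is withdrawn. This is possible, but the request for a primary reason in the same section points to the broad sense, and the text does not settle it.
- **The first alert would usually precede the exit.** The SAE behind a termination occurs before it and is reportable under sections 7.2 and 8, and an unexpected hospitalisation may already have triggered an alert. Section 8 also requires the decision to be discussed in advance with the trial director, which may make same-day exits uncommon. This limits what is lost to the outcome of the event and any later trigger event.
- **The secondary endpoints are not shown to be harmed.** Mortality and "30-day survival/hospital survival" are secondary target parameters in section 2.2, and a reader might infer that they become unknown after exit. The section 8 sentence covers safety-relevant data and sets no rule for these endpoints. Death is a recorded reason for drop-out, and insurer data supplement the study data. Whether insurer data continue after exit is not stated, so a loss is not established.

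**Conclusion.** The point holds as a defect in how section 8 is worded. It sets one end point for safety collection and reporting at every early exit and does not separate withdrawn consent from termination for an SAE or lack of compliance. The outcome of an SAE that caused the exit therefore falls outside the stated collection period. So does an unexpected death or unexpected hospitalisation after exit but within the 24-hour window, although section 7.1 requires the Board to be told of it.

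This rests on reading withdrawal as any early exit. On the narrow reading, the SAE follow-up gap for terminations by the investigator disappears, and the direct conflict is confined to consent withdrawn within 24 hours of a teleconsultation. The sentence would then still need to say so.

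The direct conflict is narrow and its frequency is unknown. The effect is on safety ascertainment; sample size and the primary analysis are unaffected.

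Two further inferences are tempting and are not supported. One is that all losses fall on the intervention side. Section 6 places tele visits in the intervention phase, so that is true of the 24-hour triggers, but section 8 applies in every phase and an SAE-driven exit can also occur under control. The other is that one or two missed events could change the Board's judgement. The protocol gives no expected number of triggers and no threshold for the Board against which to test that.

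**What to change.** Reconcile sections 7.1, 7.2 and 8:

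- In section 8, limit the cut-off for safety collection and reporting to withdrawal of consent to further data use.
- For all other exits, state that an SAE open at exit is documented to its outcome, and that section 7.1 trigger events are reported for the full 24-hour window after the last teleconsultation.
- In sections 7.1 and 7.2, add a cross-reference to this rule, so that it is clear what applies after an exit.

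The fix concerns which data are collected and reported, and leaves the criteria for ending participation as they are. Vital status at day 30 is not needed to repair this defect.

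The cost is more than an edit to one sentence. Version 03 is dated 15.02.2022, after data collection began on 01.05.2021 and after the first cluster's intervention start on 1 February 2022. Sections 11.1 and 11.4 require ethics approval for such a change. The consent form may need an update, and section 11.2 provides for a newly signed form in that case; the consent pages are not available here, so they may already cover data use after exit. Beyond that, the change adds a few data points for a small group of residents.
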